**Figure 4 figure4:**
[figure not shown]
Simplified representation of a piecewise linear latent growth model, with latent intercept factor (I), latent slope factors preintervention (S(pre)), during the intervention (S(int)), and postintervention (S(post)), and 7 indicators Y. Error terms, correlation coefficients, and covariances are left out.

**Table 5 table5:** Growth factor estimates of 4 different latent growth models.

	Fixed loadings	Time-varying loadings
Piecewise, linear	Mean: I, S(pre), S(int), S(post) Variance: I, S(pre), S(int), S(post)	Mean: I, S(pre), S(int), S(post) Variance: I, S(pre), S(int), S(post)
Quadratic	Mean: I, S, Q Variance: I, S, Q	Mean: I, S, Q Variance: I, S, Q

###### Step 2

The effect size of both experimental interventions will be calculated according to recommendations in Feingold (2009) [95] for both primary and secondary outcomes.

###### Step 3

The proportion of participants who make clinically relevant progress on the primary outcome will be calculated for all 3 conditions; again, in an intention-to-treat analysis. Percentages and standard deviations of the reliable change index will be presented.

###### Step 4

A latent growth model will be built of the primary outcome, in which the outcome measures that have been measured at T3 will also be included, as distal outcomes of changes in the primary outcome during the first semester.

###### Step 5

A growth mixture model (GMM) will be used to further explore differences between individuals, and more specifically to identify subpopulations (latent classes) with homogeneous growth trajectories of the primary outcome within the experimental groups. The Bayesian information criterion will be used for model selection [96].

If convergence considerations allow, this model will be adjusted to allow covariance of the growth factors in order to acknowledge individual variation around the estimated growth trajectories. The trace plots will be inspected to check whether the models have converged to global solutions and a set of diverse starting values will be used. For more information on these analyses, we refer to an introduction to GMM and latent class growth analysis by Jung and Wickrama [97] and examples of similar analyses in the field of Internet interventions [98] and cancer patients [41].

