#### Pre-Analysis

##### Power Analyses

The sample size for analyses for data relating to the primary objective has been calculated for a repeated measures analysis of variance: based on an alpha of .05, a minimal detectable effect size of f2=.15, and a power of .80, a total number of 55 participants [80] is required in each group to answer the primary research question of this study in a statistically valid manner.

We expect to be able to include 330 eligible participants within a period of 2 years, based on a mean of 3.7 intakes per week for the eMBCT of the Helen Dowling Institute in 2011. An estimated attrition of 30% of the participants during both experimental interventions and 15% during the minimal intervention control condition [51] would leave us with 77 participants in each experimental group and 94 participants in the control group at T2. Again, we expect a dropout rate of 30% during the second semester. Such a dropout would leave a total of 110 participants completing each experimental intervention. Ten percent of the participants may have to be excluded from the analyses because of recurrence or diagnosis of metastasis. That would result in 198 participants that complete the full trial. We expect that this number will be enough for testing the 6 mediating factors or effect predictors: A classical, conservative power calculation (analysis of variance for testing 6 mediators or effect predictors with an intermediate effect size (f2=.08), corrected according to Bonferroni (alpha=.05/6), and at a power of .80 [81]) would result in approximately 254 participants being needed. We expect that the actual power when including 198 participants, and not the required 254 participants, will be great enough to detect up to 6 mediators or effect predictors with the use of Bayesian statistics [76]. Bayesian statistics allow analysis on small sample sizes [76,77], as more power can be generated with the use of prior information which is incorporated in the model that is being tested. Various papers describe comparisons between traditional null hypothesis testing and Bayesian estimation [82-85]. For this study, prior knowledge is available for many parameters, such as the effects of mindfulness in cancer survivors [23,25,66,86] and the role of working alliance in online interventions [87]. Examples of these methods can be found in both applied psychology and social science articles [88-92].

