#### Core Analysis

##### Effectiveness

###### Overview

Five steps will be taken to evaluate the effectiveness of both interventions, which are explained here in a generic way. The specific hypotheses on the effectiveness of the interventions in our study are shown in Textbox 1.

Hypotheses on effectiveness.
*Primary outcome*
In both experimental conditions:Fatigue severitydecreases during the intervention, andremains decreased after 6 months.After 6 months, fatigue severity has decreased significantly more compared to the control condition.After 6 months, more participants show a clinically relevant reduction of fatigue severity compared to the control condition. A patient is considered clinically improved if he or she has a reliable change index of more than 1.96, according to the reliable change index, and the end score has to be within the normal range, that is a score < 1 standard deviation above the mean of a normative group [94] (ie, a score < 30.4 on the CIS fatigue severity subscale [51]).
*Secondary outcomes*
For both interventions we expect that:After 6 months, mental health and work ability have improved more than in the control condition.After 12 months, fatigue severity, work ability, and mental health remain improved in both intervention groups.Improvements in mental health and work ability after 6 and 12 months are related to reductions in fatigue severity.Return to work and reduced absenteeism will be studied as explorative outcomes.

###### Step 1

Overall effectiveness will be tested in an intention-to-treat analysis by a multiple group latent growth model [79] using data from the first semester. This technique allows individuals to have an individual growth trajectory over time and compensates for missing data in an elegant way.

Since different growth patterns are expected for the pre-intervention period, the intervention period, and the post-intervention period, we will apply piecewise growth modeling so that a slope factor will be estimated for each of the 3 periods (Figure 4). Initial intercepts will be configured to represent the T0b score. This intercept and the pre-intervention slope factor will be constrained to be equal between all 3 conditions (and this assumption will be checked), whereas the subsequent slope factors will be estimated separately for the 3 conditions.

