The fit of the piecewise model will be compared with a quadratic model. In the quadratic model, the entire first semester is modeled with 1 slope factor and 1 quadratic factor for each of the 3 conditions and an intercept that represents T0b and is constrained similarly to the piecewise model.

Both models will be run both with and without using time-varying loadings in order to check whether corrections should be made for differences in timings between the questionnaires. Growth factor estimates and model fits for all 4 models will be reported (Table 5).

Neither the participants nor the researchers ([name] and MW) are blinded to allocation. Therefore, an independent statistician ([name]) who is blind to the allocation will test the primary hypothesis.

The same procedure will be followed for the secondary outcomes, except that the initial intercept of mental health will represent T0a, rather than T0b, because T0b does not include an assessment of mental health.

Results of frequentist analyses will be reported by *P*-values (significant in case <.05) and with 95% confidence intervals. Parameter estimates of models by means of Bayesian estimators will be reported with 95% central credibility intervals.

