## Discussion

### Principal Findings

This paper has described the design, hypotheses and analysis plan of a randomized controlled trial in order to study the effectiveness, mediation, and effect predictors of 2 Internet-based interventions for CCRF. Although recruitment and inclusion have already started, publishing the analysis plan is of great value because it will help to prevent outcome reporting bias [110] and adds validity information to the final studies [111].

By using multiple assessments during the intervention, the proposed trial design is suitable for studying the chronological development of both potential mediators and fatigue. That has 2 main advantages. Firstly, the data will be suitable for analyses that allow for variation in the individual fatigue trajectories. We do not expect that either of the interventions that have been included in the trial will be beneficial for all participants: our study sample will be highly heterogeneous considering for example tumor and treatment types. Therefore, the analyses on individual growth trajectories can acknowledge that expectation and test that hypothesis. This will substantiate the interpretation of the results on effectiveness and will be an important first step in identifying what works for whom. Secondly, this study design enables us to use a fully longitudinal mediation analysis, at least for the most important factors, rather than using indirect effects analysis in cross-sectional mediation analysis.

Another important feature of the proposed design is that by comparing 2 different interventions with an active control group, therapy-specific elements of the interventions can be distillated from the data acquired during this trial. This advantage counts for both the effect predictors and the mediators. Knowledge about such differentiating factors can and should be used to better inform patients with CCRF and to improve allocation of patients with CCRF to suitable interventions. As a result, an increase in the overall effectiveness of relevant interventions can be established.

In this paper, we have presented the trial design, our hypotheses, and a detailed analysis plan. In accordance with good clinical practice, and to avoid outcome reporting bias, this paper was submitted before any of the data was analyzed. All methods are now openly predetermined, therefore any future publication describing this trial can be valued reliably on its quality.

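### Textbox 1 states a comparative responder hypothesis under Primary outcome, but Step 3 only tabulates percentages per arm, which cannot separate a real excess over control from chance

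*Protocol article*

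**What the plan says.** The hypotheses are in Textbox 1 of the protocol article (Analysis Plan, Core Analysis, Effectiveness). Those under Primary outcome are introduced as applying to both experimental conditions. One concerns mean change: "fatigue severity has decreased significantly more compared to the control condition". The next concerns responders: "After 6 months, more participants show a clinically relevant reduction of fatigue severity compared to the control condition". A responder is someone who "has a reliable change index of more than 1.96" and whose end score on the CIS fatigue severity subscale is below 30.4.

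Step 3 gives the analysis of responders: "The proportion of participants who make clinically relevant progress on the primary outcome will be calculated for all 3 conditions", by intention to treat. Its output is then stated: "Percentages and standard deviations of the reliable change index will be presented".

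A general reporting rule at the end of Step 1 says that frequentist results come with P-values ("significant in case <.05) and with 95% confidence intervals"). The Discussion says of the plan as a whole: "All methods are now openly predetermined".

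**The concern.** The hypothesis compares arms and its analysis describes them one at a time. Three percentages carry no measure of the uncertainty in the difference between any two of them, so they cannot show whether an intervention truly produces more responders than control. The responder hypothesis also lacks the word 'significantly' that the mean-change hypothesis carries, which leaves room to count any numerical excess as support.

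At stake is one of the claims listed under Primary outcome, and the one that readers in practice may find easiest to use. If the contrast is not fixed now, its form and the treatment of missing T2 scores would be chosen later by researchers who, as Step 1 says, are not blinded to allocation.

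**Working it through.** **1. Does another step supply the comparison?**
- Step 1 tests growth factors of the continuous score.
- Step 2 gives effect sizes for the primary and secondary outcomes and names no responder contrast.
- Step 4 adds T3 measures as distal outcomes.
- Step 5 looks for latent classes within the experimental groups.
- The reporting rule in Step 1 says how frequentist results are shown, but no frequentist comparison of responders is defined for it to act on.

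So Step 3 stands alone.

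**2. Arm sizes at 6 months.** From Power Analyses: 330 / 3 = 110 per arm; 110 × 0.70 = 77 in each experimental arm; 110 × 0.85 = 93.5, rounded to 94 in control. This reproduces the plan's 77, 77 and 94. The sample size calculation ("based on an alpha of .05, a minimal detectable effect size of f2=.15, and a power of .80") is for a repeated measures analysis of variance. No power is given for the responder comparison.

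**3. Chance of a numerical excess when there is no effect.** The documents give no responder rate, so I assume one rate *p* in all arms and show 10% to 40%. With A and B the numbers of responders in the two experimental arms and C the number in control, all independent binomials, the probabilities are:
- a given arm higher: P(A/n_A > C/n_C)
- at least one arm higher: the same event for A or B
- both arms higher: the same event for A and B

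| Arm sizes | p | Given arm higher | At least one | Both |
|---|---|---|---|---|
| 77/77/94 | 10% | 49% | 66% | 32% |
| 77/77/94 | 20% | 50% | 67% | 32% |
| 77/77/94 | 30% | 50% | 67% | 32% |
| 77/77/94 | 40% | 50% | 68% | 32% |
| 110 per arm | 10% | 46% | 62% | 29% |
| 110 per arm | 20% | 47% | 63% | 30% |
| 110 per arm | 30% | 47% | 64% | 30% |
| 110 per arm | 40% | 47% | 64% | 31% |

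The row that matches Textbox 1 most closely is 'both', since the hypothesis is stated for both experimental conditions. At 77/77/94, both arms exceed control by 5 points or more in 4% to 12% of trials (8% at *p* = 20%). A given arm does so in 14% to 25%.

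**4. What an interval would show.** Take an observed 23/77 (29.9%) against 19/94 (20.2%), a difference of 9.7 points. The Wilson 95% limits are 20.8% to 40.8% and 13.3% to 29.4%. Newcombe's interval for the difference is:
- lower: 9.7 − √[(29.9 − 20.8)² + (29.4 − 20.2)²] = −3 points
- upper: 9.7 + √[(40.8 − 29.9)² + (20.2 − 13.3)²] = 23 points

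As bare percentages, 30% against 20% looks like support. The interval includes zero.

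**5. Precision to expect.** The approximate half-width is 1.96 × √[p(1 − p)(1/77 + 1/94)]. At *p* = 10% this is 1.96 × √(0.09 × 0.02362) = 9.0 points. At *p* = 40% it is 1.96 × √(0.24 × 0.02362) = 14.8 points.

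**The case against.** The best defence is that Step 3 is meant as a supporting description of clinical relevance. Overall effectiveness is tested in Step 1, and the blinded statistician tests a single primary hypothesis there. The article says that its steps are explained generically, and naming a two-proportion test is detail that a fuller plan would often hold. The reporting rule in Step 1 may also have been intended to cover Step 3.

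Part of this stands. The trial's main conclusion does not rest on Step 3, and that limits the weight of the point. The rest does not remove it. The article presents itself as the analysis plan with its methods already fixed. It does not merely leave the output of Step 3 open: it states an output, and that output cannot answer the hypothesis. If the analysis is only descriptive, a comparative hypothesis under Primary outcome is mislabelled.

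A reader might also infer more than the text supports:
- **That a chance excess would be taken as confirmation.** No rule in the document says so. It could be read that way, no more.
- **That the false-support rate is the 66-68% for at least one arm.** Textbox 1 speaks of both experimental conditions. For the joint claim the figure is about 32%.
- **That the sizes reported in Results for January 2015 (36, 24 and 32) make matters worse.** They are an enrolment snapshot with recruitment still open. No analysis is planned at those numbers.
- **That 77/77/94 is the analysis set.** Step 3 is by intention to treat, and those are the numbers left after attrition. Depending on how missing T2 scores are handled, the analysed numbers could be as high as 110 per arm, where the figure for both arms is 29-31%.

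**Conclusion.** The point holds. The responder hypothesis in Textbox 1 is comparative, and the only analysis given for it has no contrast between arms. With equal true rates, both interventions would show a numerically higher percentage than control in roughly three trials in ten, and a given intervention in about half. These figures rest on an assumed common rate of 10% to 40%, independent arms, and sizes between 77/77/94 and 110 per arm; they change little across those ranges. They show what bare percentages cannot exclude. They are not the error rate of a decision rule, because the plan states none. Step 1 and the mean-change hypothesis are untouched, so this should be corrected but does not threaten the trial's main result.

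**What to change.** Add to Step 3: for each intervention against control, estimate the difference in the proportion clinically improved at T2 with its 95% confidence interval in the intention-to-treat set. Call the Textbox 1 hypothesis supported for that intervention only if the interval excludes zero in its favour. Keep the percentages and the RCI standard deviations as description. In the same place, state how participants without a T2 score enter the proportion, since expected attrition is 30% in the experimental arms and 15% in control. Adjustment for the T0b CIS score is optional. If the authors want no formal comparison, they should instead label the hypothesis as descriptive.

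The cost is a sentence or two and one small analysis on data already being collected. The drawback is limited precision. With intervals about 9 to 15 points either side, the hypothesis may end up unsupported even if a moderate effect exists. At 94 against 77, two-sided alpha .05 and an assumed control rate of 10% to 30%, power is 28% to 46% for a 10-point difference and 76% to 91% for 20 points. Per-arm percentages would leave that uncertainty unseen.

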##### Effect Predictors

###### Overview

Two complementing approaches for analyzing the effect predictors are addressed in steps 8 and 9 of this analysis plan. The specific hypotheses on the effect predictors for both interventions in this particular study are shown in Textbox 3. 

Hypotheses on effect predictors.We expect that for AAF, low perceived physical activity predicts reduction of fatigue severity.We expect that for eMBCT, low perceived concentration, previous experience with mediation exercises, high perceived life threat from cancer, and a high education level predict reduction of fatigue severity.In general, we expect that low perceived social support, longer time since last treatment, suffering from more comorbidities [108], and having strong somatic attributions [57] predict small effects on fatigue severity in both interventions. We expect that high sense of control and good sleep quality predict large effects in both experimental conditions.Other factors will be included for explorative research.

###### Step 8

To find out which participants benefit most from each intervention, the final model of fatigue severity of Step 1 will be extended with potential effect predictors (Textbox 3) that load on the latent growth factors “linear slope” (the “post randomization” linear slope in case of the piecewise model) and, if applicable, “quadratic slope.” As the regression coefficients of all potential effect predictors on the development of fatigue severity will be freely estimated across the 3 intervention groups, this is also called a moderation effect of intervention.

Factor loadings of all hypothesized effect predictors will be reported. Those with the highest loadings will be compared between the conditions in order to find differential effect predictors.

###### Step 9

To identify common effect predictors of homogeneous subpopulations within the heterogeneous population, rather than identifying effect predictors for individual growth patterns, the final step will consist of regressing predictors on latent classes. Therefore, the final model of Step 5, the GMM, will be extended. Again, several potential effect predictors will be regressed onto this model, but this time on the latent class factor, instead of on the latent growth factors. The 3-step procedure proposed by Vermunt [109] will be used for model selection. This step will be carried out separately for each experimental condition.

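### Step 5 lets convergence decide whether latent classes allow individual variation; if the version without it decides, BIC will usually find subpopulations in one continuous population

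*Protocol article*

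**What the plan says.** Core Analysis, Effectiveness, Step 5 gives the growth mixture model an exploratory role: it "will be used to further explore differences between individuals" and is meant to "identify subpopulations (latent classes) with homogeneous growth trajectories of the primary outcome within the experimental groups". The only selection rule is "The Bayesian information criterion will be used for model selection". The next paragraph adds "If convergence considerations allow, this model will be adjusted to allow covariance of the growth factors in order to acknowledge individual variation". For convergence, trace plots are inspected and "a set of diverse starting values will be used".

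Two other places bear on this:

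- Step 1 already assumes that patients differ: "This technique allows individuals to have an individual growth trajectory over time". Table 5 lists a variance for the intercept and for every slope.
- In Step 9, "the final model of Step 5, the GMM, will be extended", and "the final step will consist of regressing predictors on latent classes", separately for each experimental condition. The strongest predictors are then compared between conditions.

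The article does not say whether BIC is applied again after the adjustment, whether a one-class growth model with individual variation is among the candidates, or what is reported if the adjusted model fails to converge.

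**The concern.** Step 5 asks whether an arm contains distinct subpopulations. The null for that question is one population whose members differ by degree, which is the Step 1 model. If the starting mixture has no variation inside a class, its one-class version says something else: every patient in the arm follows the same trajectory apart from independent residuals. BIC then weighs any individual variation against none. Extra classes win because they are the only way that model can absorb differences between patients.

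The plan leaves two routes by which such a model can fix the number of classes. The adjusted model may not converge, or the class count may be carried over to it without a new enumeration. In either case slices of a continuum could be reported as subpopulations, and Step 9 would attach predictors to them. Diverse starting values and trace plots protect against local optima, not against this.

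**Working it through.** **Inputs from the article.** Figure 4 gives seven indicators and a piecewise model with an intercept and three slopes. The outcome is the CIS fatigue severity subscale, range 8–56, with entry at 35 or higher. Step 5 states no figure of its own, so its sample size comes from Power Analyses: 330/3 = 110 per arm, and 110 × 0.70 = 77 per experimental arm at T2, which reproduces the stated 77. The January 2015 group sizes were 36 (AAF) and 24 (eMBCT), mean 30. The check therefore uses n = 30, 77 and 110.

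**Assumed, not in the documents.** Intercept SD 3–6 points, SD of change over the intervention 3–6, SD of later change 2–4, residual SD 4–5, mean change −7.

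**Why the reference matters.** Without within-class variation, the one-class model implies zero correlation between T0a and T0b. In the simulated base case (intercept SD 5, residual SD 4) that correlation is 25/(25 + 16) = 0.61. In the low-heterogeneity case (3 and 5) it is 9/(9 + 25) = 0.26.

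**Models compared.** BIC = −2 log L + p ln n, with K classes and four growth-factor means per class:

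- (a) no within-class variation, seven time-specific residual variances: p = 4K + (K − 1) + 7, K = 1–5
- (b) variances free, covariances zero, one residual variance: p = 4K + (K − 1) + 5, K = 1–3
- (c) full covariance matrix equal across classes, one residual variance: p = 4K + (K − 1) + 11, K = 1–3

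Model (c) with K = 1, the one-class growth model, has 4 + 0 + 11 = 15 parameters. Model (a) has 8 + 1 + 7 = 16 at K = 2 and 20 + 4 + 7 = 31 at K = 5. The class solutions therefore win against their own one-class version, not by being more economical than a growth model.

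**Result.** Share of 60 data sets per row, all drawn from one population (true K = 1), in which BIC chose two or more classes:

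| n | Data | (a) none | (b) variances only | (c) full covariance |
|---|---|---|---|---|
| 30 | base | 100% | 0% | 0% |
| 30 | low heterogeneity | 88% | 10% | 0% |
| 77 | base | 100% | 0% | 0% |
| 77 | intercept–slope correlation −0.4 | 100% | 10% | 0% |
| 77 | low heterogeneity | 100% | 2% | 0% |
| 77 | bounded 8–56, entry ≥ 35 | 100% | 0% | 0% |
| 77 | skewed change | 100% | 15% | 13% |
| 110 | base | 100% | 0% | 0% |
| 110 | low heterogeneity | 100% | 0% | 0% |

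In the base case at n = 77, model (a) chose 3, 4 and 5 classes in 3, 22 and 35 of the 60 data sets (5 was the maximum fitted). With 60 data sets, an observed 0% has a one-sided 95% upper limit of 1 − 0.05^(1/60) = 4.9%. A shorter run of 25 data sets gave 20% for (c) with skewed change, where the 60 gave 13%.

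**Two further simulations, also with assumed SDs.** One used six scores and 40 replicates per setting. Without within-class variation it gave two or more classes in 90–100% of runs at n = 77, the 90% arising when all growth-factor SDs were only 2 points. With a common within-class covariance it gave 0–17.5% over n = 40, 77 and 110. The other used seven indicators at n = 30–110 and gave 80–100% without within-class variation. In 70–100% of those same runs, a one-class growth model with random effects had a better BIC than every such class solution.

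**The case against.** The sentence at issue is itself a plan to relax the model, so a reader who infers that Step 5 will report false subpopulations whatever happens goes too far. If classes are counted again under the relaxed model, false classes are rare. That stands, and the point is therefore conditional.

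The starting specification is inferred. The article calls the model a growth mixture model, its Introduction says that mixture models accommodate individual variance, and what is added later is covariance. Literally, variances could already be free. Column (b) shows that this reading gives only 0–15%. Against it, the stated purpose of the adjustment is to acknowledge individual variation, which a model with free variances would already do. The ambiguity is real, and the readings give very different results.

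A reader might also infer that non-convergence is likely at 77 per arm. Nothing in the documents supports a rate. The 77 is also a completer count, and the intention-to-treat number is nearer 110. The rates in column (a) are the same at both sizes.

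Nor does the whole question of who benefits rest on these classes. Step 8 addresses it with continuous growth factors and no classes, and Step 9 is a complementary approach.

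Finally, an article may leave enumeration detail to a fuller plan. That would excuse silence, but the article states the fallback, and following it gives a misleading answer.

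**Conclusion.** The point holds in conditional form. If a class model without within-class variation decides the number of classes, BIC will report two or more subpopulations in about 80–100% of data sets from one continuous population at n = 30 to 110, and Step 9 will seek predictors of them. With within-class variation free, the rate is about 0–18%, the upper end coming from skewed change or small samples. These rates rest on assumed SDs. The contrast between the models persisted over the ranges tried, for normal, bounded and skewed data.

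The documents do not support saying that the fallback will be used or how often. They establish only that it is a stated exit and that the wording leaves the starting model open. The consequence is confined to the exploratory Step 5 and to Step 9. The primary test in Step 1 and the predictor analysis in Step 8 are unaffected. The change is worth making because it is nearly free and the text invites the error.

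**What to change.** State in Step 5 whether the starting model has growth-factor variances fixed at zero, or free variances with zero covariances. Then, for each experimental arm:

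1. Include the one-class growth model with free growth-factor variances and covariances (the Step 1 model) as the K = 1 reference in the BIC comparison.
2. Repeat the class enumeration with within-class variation free, for example with a class-invariant covariance matrix, reduced to variances only if convergence requires it. The reference alone is not enough: in up to 30% of runs it did not beat every class solution without within-class variation.
3. Claim subpopulations and run Step 9 only where a solution from that enumeration with K of 2 or more beats the reference on BIC.
4. Otherwise report the Step 1 slope variance for that arm, and label any class solution without within-class variation as descriptive only.

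The cost is a few sentences in Steps 5 and 9 and a few extra Mplus runs. The downside is that an arm may yield no classes and therefore no Step 9. Some false classes remain possible when change is skewed (13–15% in the table), so a positive result still needs cautious wording.
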